## Abstract

**Background:**

Practice guidelines recommend various types of exercise for chronic back pain but there have been few head-to-head comparisons of these interventions. General exercise seems to be an effective option for management of chronic low back pain (LBP) but very little is known about the management of a sub-acute LBP within sub-groups.

Recent research has developed clinical tests to identify a subgroup of patients with chronic non-specific LBP who have movement control dysfunction (MD).

**Method/Design:**

We are conducting a randomized controlled trial (RCT) to compare the effects of general exercise and specific movement control exercise (SMCE) on disability and function in patients with MD within recurrent sub-acute LBP. The main outcome measure is the Roland Morris Disability Questionnaire.

**Discussion:**

European clinical guideline for management of chronic LBP recommends that more research is required to develop tools to improve the classification and identification of specific clinical sub-groups of chronic LBP patients. Good quality RCTs are then needed to determine the effectiveness of specific interventions aimed at these specific target groups. This RCT aims to test the hypothesis whether patients within a sub-group of MD benefit more through a specific individually tailored movement control exercise program than through general exercises.

## Background

### LBP epidemiology

LBP is a common, costly problem, often associated with high recurrence rates and equivocal management efficacy [1,2]. LBP remains the primary cause of absenteeism and disability in every industrialized society [3].

Patients who develop chronic LBP (pain and disability persisting for more than 3 months) use more than 80% of all health care for back pain [3].

A recent systematic review of the prognosis of acute LPB showed that the view of spontaneous healing is inaccurate. Pain and disability are typically ongoing, and recurrences are common. Up to 70% of those who initially improve, experience repeated fluctuating pain episodes [4]. Thus, effective treatments for patients whose pain and disability persist beyond the acute phase are needed.

We are interested in the sub-acute phase, which is the transition period from acute (duration less than 6 weeks) to chronic (duration over 3 months) LBP.

The European Guidelines for Management of Chronic Non-Specific LBP recommend supervised exercise therapy as a first-line treatment for chronic LBP [5]. Exercise therapy appears to be slightly effective in decreasing pain and improving function in adults with chronic LBP, particularly in healthcare populations. In sub-acute LBP there is evidence that a graded activity program improves absenteeism outcomes, though evidence for other types of exercise is unclear [6,7].

A cost effectiveness study compared the costs and benefits of a graded activity intervention

To usual care for sick-listed workers with nonspecific sub-acute LBP. After a 3-year follow-up it could be concluded that the graded activity intervention for non-specific LBP is a cost-beneficial return-to-work intervention [8]. An RCT compared the effects of stabilizing training and manual therapy in sub-acute and chronic LBP. The results did not indicate any clear short-term differences between the groups in the accessed outcome measures. In the long term, however, stabilizing training seemed to be more effective than manual treatment in terms of improvement of individuals and the reduced need for recurrent treatment periods [9]. Another RCT indicated that in participants with sub-acute LBP, physiotherapist-directed exercise and advice were each slightly more effective than placebo at 6 weeks. The effect was greatest when the interventions were combined. At 12 months, the only effect that persisted was a small effect on participant-reported function [10].

A few studies have tried to find out the prognostic factors and the transition from acute or sub-acute LBP to chronic pain. A prospective cohort study of patients with episodes of acute or sub-acute LBP, seeking physical therapy in primary care, with follow-up at weeks 2, 4, 8, and 12 strongly revealed pain-related items to be essential factors in the development of chronic and long-term disability in primary care physical therapy. Health status at 8 weeks seemed crucial in developing chronic pain [11]. A Dutch cluster RCT provided no evidence that general practitioners should adopt a new treatment strategy aimed at psychosocial prognostic factors in patients with sub-acute LBP [12].

A prospective cohort study demonstrated that physical parameters did not have a prognostic value with regard to outcome of treatment. Furthermore, the data confirmed that

Patients' subjective estimation of pain and disability already displays a prognostic value for therapy outcome that cannot be increased significantly by the assessment of physical parameters [13].

Chronic non-specific LBP has been studied with many exercise interventions. The types of exercise programs for chronic LBP vary widely e.g. land-based exercise versus exercise in water, individual exercise versus group exercise, isolated trunk exercise versus whole body exercise. Unfortunately there is little or no evidence to help clinicians select the most effective type of exercise for an individual patient. This absence of evidence means that care is likely to be sub-optimal. While some trials of exercise have reported large, durable and clinically important effects [14], others have not [15]. The types of exercise programs, and patient presentations for chronic LBP vary widely so it is unlikely that all programs are equally effective for all patients[6].

### General exercise and standard therapy

There is not a 'standard therapy' for any type (acute, sub-acute, chronic) of LBP that is agreed upon to use as a comparison in clinical trials. Exercise therapy is recommended by various guidelines [5,16], but it is not clear which type of exercises are best.

The use of general exercise is problematic because there are so many types of exercise that may be considered under this umbrella term [17].

One study [18] compared general exercise, motor control exercise and manual therapy in treating chronic LBP. Cardiovascular aerobic and main muscle group strengthening exercises were considered general exercise. Muscle strengthening exercises were conducted with weights. Koumantakis et al. (2005) defined general exercise as targeting abdominal and paraspinal muscles without the involvement of the deep muscles activation [19]. A systematic review by Keating et al. (2006) referred to general exercise as muscle strengthening, coordination and aerobic fitness improving exercises [20]. The same approach had been used by Dvorak et al. (2001) [21]. Classic trunk exercises performed in physical therapy activate the abdominal and paraspinal muscles as a whole and at a relatively high contraction level [22,23].

As a conclusion the term general exercises can involve strengthening exercises for all the main muscle groups with or without the addition of weights. In addition, the term can involve exercises improving coordination, stretching and aerobic fitness training.

According to the literature, general exercises seem to be an effective treatment for non-specific LBP in physiotherapy. The benefits include: pain reduction, improved working ability, increased function, reduced depression and reduced fear of pain. However, the results are comparable to those with specific exercise, especially in the longer term. The short term benefits for specific training methods are potentially even more effective in reducing pain [18,24-30].

### Sub-classification of low back pain patients

The heterogeneity of the patients with non-specific LBP has been problematic. The sub-grouping these patients was declared to be one of the main focuses for future research a decade ago. Emphasis is to view LBP as a multi-factorial biopsychosocial pain syndrome [31].

A systematic review with a meta-analysis has been published to determine the integration of sub-classification strategies with matched interventions in RCTs evaluating manual therapy treatment and exercise therapy for chronic non-specific LBP. Only 5 of 68 studies (7.4%) sub-classified patients beyond applying general inclusion and exclusion criteria. In the few studies where classification and matched interventions have been used, meta-analysis showed a statistical difference in favour of the classification-based intervention for reductions in pain (both for short-term and long-term) and disability. Effect sizes ranged from moderate (0.43) for short term to minimal (0.14) for long term. The authors concluded that a better integration of sub-classification strategies in chronic non-specific LBP outcome research is needed. They proposed the development of explicit recommendations for the use of sub-classification strategies and evaluation of targeted interventions in future research evaluating chronic non-specific LBP [32].

Another systematic review [33] tried to determine the efficacy of targeted treatment for sub groups in adults with non-specific LBP. The results provide cautious evidence supporting the notion that treatment targeted to subgroups of patients with non-specific LBP may improve patient outcomes. However, the results of the studies included in this review are, inconsistent and the samples investigated are too small to make recommendations for clinical practice. The research suggests that adequately powered clinical trials using designs capable of providing robust information to support the modification of clinical practice are uncommon. Considering how central the notion of targeted treatment is to manual therapy principles, further studies using this research method should be a priority for the clinical and research communities.

A recent study emphasized stratification of management according to the patient's prognosis (low, medium, or high risk). They compared the clinical effectiveness and cost-effectiveness of stratified primary care (intervention) with non-stratified current best practice (control). 851 patients were assigned to the intervention (n = 568) and control groups (n = 283). Overall, adjusted mean changes in RMDQ scores were significantly higher in the intervention group than in the control group at 4 months and at 12 months. At 12 months, stratified care was associated with a mean increase in generic health benefit cost savings compared with the control group. The results suggest that a stratified approach, by use of prognostic screening with matched pathways, may have important implications for the future management of back pain in primary care[34].

#### Movement control

The importance of sub-classification has been highlighted in several studies. When sitting postures are compared between pain free subjects and patients with LBP, there are no significant differences [35-37]. However, when the patients are sub-classified into flexion and active extension control impairments, then the differences are significant. The direction of the movement control defines the way patients sit [37] and the activity in their back muscles; the flexion group has less back muscle activity and the active extension group more [36].

The MD is a clear subgroup of non-specific LBP. Pathokinesiologic movement patterns in the lumbar spine have been investigated and described [38-42].

Scholtes et al. [43] compared two groups of people who played rotation-related sports and their capability to control lumbar spine movement during knee flexion lateral hip rotation. The interpretation of that study was that patients with LPB have poorer control of their lumbopelvic movements, and because of this, might be moving in their daily activities and sports more on their lumbar spine which may cause pain. A significant difference in the ability to actively control the movements of low back between patients with low back pain and subjects without back pain has been demonstrated by Luomajoki et al. [44]. The effect size between patients with LBP and healthy controls in movement control is large.

The reliability of tests to diagnose MD has been shown to be acceptable. Dankaerts et al. [45] reported an almost perfect agreement (k = 0.96 and percentage agreement 97%) between two expert examiners rating a motor control dysfunction classification. Van Dillen et al. [46] used a battery of physical examination items in order to categorize the patients in an impairment dysfunction subgroup. They found a very high agreement for the assessment of symptoms among the examiners (k > 0.89 and percentage agreement > 98%). Luomajoki et al. [47] examined ten movement control tests for the back. Four blinded physiotherapists evaluated subjects through observation of videos. For the intraobserver reliability, five tests out of ten showed an excellent reliability (k > 0.80). Four further tests had a substantial reliability (k = 0.6-0.8) and one was moderate (0.51). Five out of ten tests showed a substantial inter-observer reliability (k > 0.6), four tests had Kappa values between 0.4 and 0.6 (good) and one test was under 0.4 (fair). The percentage agreement varied between 65% - 97.5%. White and Thomas [48] investigated the reliability (N = 37) of 16 tests of the Movement System Balance approach developed by Sahrmann [49], finding a satisfactory reliability between raters.

Harris-Hayes and van Dillen found overall percent agreement on the classification assigned to be 83% with kappa = 0.75 (95% confidence interval = 0.51-0.99; *P *< .0001) and concluded that inter-tester reliability of classification of patients with LBP when therapists use a standardized clinical examination based on the Movement System Impairment classification system is substantial [50]. Trudelle-Jackson et al. (2008) showed that interrater reliability between two physical therapists classifying patients with chronic LBP into 1 of 5 lumbar spine movement impairment categories had substantial agreement [51].

One recent study analysed the reproducibility of five different quantitative tests for those commonly used in daily clinical practice. These five tests for lumbar movement control displayed excellent reproducibility. There is no gold standard for movement control, therefore there are no diagnostic accuracy statistics available for these tests. The diagnostic accuracy of these tests needs to be addressed in larger cohorts of subjects, establishing values for the normal population. Also cut off points between subjects with and without LBP must be determined, taking into account age, level of activity, degree of impairment and participation in sports [52].

We are using the model presented by O'Sullivan [53]. In this classification of chronic LBP pain disorders, sub-groups, based on the mechanism underlying the disorder, are considered critical to ensure appropriate management. It is proposed that three broad sub-groups of chronic LBP disorders exist. In the first group of disorder patients present underlying pathological processes driving the pain, and the patients' motor responses in the disorder are adaptive. A second group disorders patients show psychological and/or social factors representing the primary mechanism underlying the disorder that centrally drives pain, and where the patient's coping and motor control strategies are mal-adaptive in nature. Finally it is proposed that there is a large group of chronic LBP disorders where patients present with either movement impairments (characterized by pain avoidance behaviour) or control impairments (characterized by pain provocation behaviour). These pain disorders are predominantly mechanically induced and patients typically undertake mal-adaptive primary physical and secondary cognitive compensations for their disorders that become a mechanism for ongoing pain. These subjects present either with an excess or deficit in spinal stability, which underlies their pain disorder[45].

#### Specific movement control exercises

The underlying hypothesis is that, due to poor MD of the back, the person is unknowingly damaging him- or herself through faulty movement patterns. O' Sullivan [53] describes these back pain patients not as pain avoiders, but, as pain provocateur. Relative flexibility theory [50] suggests that movement occurs through the pathway of least effort, e.g. if the hip movement is relatively stiff compared to that of the low back, then the movement is more likely to happen in the back, leading to a back pain problem related to the direction of that particular movement.

The directions or symptoms of the movement control are called flexion, extension and sideflexion/rotation.

To rehabilitate this type of MD, specific movement control exercises (SMCE) have been suggested [49]. These are exercises in which one joint (or region) is maintained in a neutral position with conscious control, either while an adjacent joint (or region) is independently moved, or while performing part of a functional movement, with normal breathing. The exercises require more sensory motor awareness and neurocognitive function to perform than general exercise [54]. They are generally performed with slow, low force repetitive movements. They can be performed with high load or with speed, however it is recommended that this is included in the description of the exercise protocol [Gibbons SGT, Newhook TW 2011 Specific movement pattern control exercise for low back pain: A systematic review. Submitted].

Evidence is gradually accumulating for the use of SMCE. A recent systematic review identified six randomized controlled trials, one prospective cohort study, one case control study, one case series and seven case studies that used SMCE. Based on four high quality RCT, the following levels of evidence were found: there is moderate evidence from one study for a long term (12 months) benefit of disability, pain and fear for the use of SMCE when combined with another form of active treatment and education for chronic LBP; there is moderate evidence from two studies for a short term (6 weeks) benefit of pain, pain interference and disability, for the use of SMCE when combined with active and passive treatments for chronic LBP; there is moderate evidence from one study for medium term (6 months) benefit of pain, disability and quality of life for the use of SMCE when combined with active and passive treatments for a mixed group of sub-acute and chronic LBP [Gibbons SGT, Newhook TW 2011 Specific movement pattern control exercise for low back pain: A systematic review. Submitted].

The clinical trials in this review used subjects with mostly chronic LBP. There is a need for knowledge of this type of intervention in sub-acute LBP.

### The aim of the study

The purpose of this study is to compare individually tailored SMCE to general exercise for reducing disability in patients with recurrent, sub-acute non-specific LBP after they have been sub-classified with MD.

## Methods/Design

The study protocol was registered on 18^th ^January 2012, registration number ISRCTN48684087 and approved by the Ethics Committee of Carea (Kymenlaakso Hospital District, Finland) in 17^th ^May 2010.

### Participants

#### Recruitment

Participants are 70 patients seeking treatment for sub-acute non-specific LBP from one physical therapy clinic in Kotka, Finland, between October 2010 and November 2012 (estimation).

#### Inclusion criteria

To be eligible for inclusion patients had to have non-specific LBP for at least 6 weeks, be aged between 16 and 65 years, and give written informed consent. Participants should have had at least one episode of LPB prior to the study. The aim of the rest inclusion regimen is to sub-classify those patients who have MD.

The participant should score Roland-Morris Disability Questionnaire [55] to be ≥ 5 points, DEPS [56] < 12 points, Tampa Scale for Kinesiophobia [57] < 38 points and Motor Control Abilities Questionnaire < 80 points. The Motor Control Abilities Questionnaire (MCAQ) is a self report tool that was developed to screen people for their ability to learn specific motor control stability exercise and specific movement control exercise. Reliability and validity have been established. A cut off point of 80 has a specificity of 0.98 and a sensitivity of 0.88 [58]. The MCAQ should be used to exclude those subjects who are unable to learn the exercises and thus not benefit from the treatment [59].

Within the physical examination the participant should have ≥ 2/6 positive MD test described by Luomajoki et al. [47]; should not have Straight Leg Raise (SLR) under 50° or any positive sacroiliac-joint pain provocation tests [60] to be eligible to participate in the study. Clinical assessment should indicate that the subject is suitable for active exercise, which is asked within a questionnaire.

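### The duration criterion has a 6-week floor but no ceiling, so a trial described as sub-acute does not exclude patients whom the protocol itself calls chronic

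*Protocol article*

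**What the plan says.** The Background (LBP epidemiology) of the protocol article defines the phase of interest as the "sub-acute phase, which is the transition period from acute (duration less than 6 weeks) to chronic (duration over 3 months) LBP". The stated aim is "reducing disability in patients with recurrent, sub-acute non-specific LBP after they have been sub-classified with MD". The Recruitment section uses the same label: "Participants are 70 patients seeking treatment for sub-acute non-specific LBP from one physical therapy clinic". The Discussion, including its limitations paragraph, again describes the population as sub-acute.

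Under Inclusion criteria, the only statement about how long the pain must have lasted is that "patients had to have non-specific LBP for at least 6 weeks, be aged between 16 and 65 years". A separate sentence covers history: "Participants should have had at least one episode of LPB prior to the study". The Exclusion criteria list neurological signs, specific spinal pathology, previous back surgery and contraindications to exercise therapy. They also explain the purpose of the questionnaires and physical tests. None of these items refers to duration.

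**The concern.** The population that the trial is described as studying has two duration limits, and the rule that decides entry has one. A screener who follows the Inclusion and Exclusion criteria has no stated ground for turning away a patient whose pain has passed 3 months, although the Background would class that patient as chronic.

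Duration matters here because it is part of the trial's rationale. The section on specific movement control exercises says that earlier trials enrolled mostly chronic patients and that knowledge is lacking in sub-acute LBP. The Discussion argues that effective treatment at this stage could avoid the cost of pain becoming chronic, and it expects the findings to carry over to similar populations. If an unknown part of the sample is already chronic, a result from the whole sample does not by itself answer the sub-acute question.

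**Working it through.** This is a comparison of texts. The protocol gives no figure on this point to reproduce.

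**Step 1: the definition (Background, LBP epidemiology).** Acute is under 6 weeks and chronic is over 3 months, so sub-acute runs from 6 weeks to 3 months. In weeks, 3 months = 3 × (365.25 / 12) / 7 = 13.0, so the window is about 6 to 13 weeks.

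**Step 2: the entry rule (Inclusion criteria).** Duration of at least 6 weeks, with no upper limit. The floor is exactly the lower bound of the definition; the upper bound has no counterpart.

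**Step 3: could another criterion supply the ceiling?**

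| Element | Limits duration from above? |
|---|---|
| Age 16 to 65, consent | No |
| At least one prior episode | No; it concerns history, not the length of the present pain |
| Cut-offs on RMDQ, DEPS, Tampa scale and MCAQ | No |
| Movement control tests, straight leg raise, sacroiliac tests | No |
| Exclusions (neurological signs, spinal pathology, surgery, contraindications to exercise) | No |
| Recruitment statement | Only through the word sub-acute; no figure given |
| Flow chart (Figure 1) | Not shown; its legend mentions no duration |

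Nothing in the available text states a ceiling. The written rule spans 6 weeks to any length, against a defined window of about 6 to 13 weeks.

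**Step 4: how many participants could be affected.** The documents give no distribution of episode duration. With an assumed share p beyond 3 months, the number outside the defined population is 70 × p:

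- p = 20%: 70 × 0.20 = 14 outside, 56 inside
- p = 40%: 70 × 0.40 = 28 outside, 42 inside
- p = 60%: 70 × 0.60 = 42 outside, 28 inside

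These shares are illustrative. The inconsistency between definition and rule does not depend on them.

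**The case against.** The strongest reply is that the criteria should not be read alone. The Recruitment section, also under Participants, limits the source to people seeking treatment for sub-acute LBP, and the Background gives that word a 3-month bound. Read together, these imply a ceiling that was simply not repeated. The document is also a journal article: the full protocol, the screening form and Figure 1 are not at hand and may carry the limit.

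Part of this stands. The intent is clear, and it cannot be said that chronic patients were or will be enrolled, only that the written rule does not exclude them. But the label does not place a limit in the criterion. Nor is this ordinary condensation: the article gives numerical cut-offs for age, four questionnaires, the movement tests and the straight leg raise, and it states the lower duration limit as a number. If the label were enough to set duration, the floor would not have been needed either.

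It is also fair to say that randomisation protects the between-group comparison whatever the mix of durations. That stands in full, and it limits the harm to the population claim.

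Two stronger readings are tempting, and the documents support neither:

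- **A first-ever episode satisfies the recurrence requirement**, because an episode already 6 weeks old began before the study. On that reading the sentence would exclude nobody, since everyone meeting the 6-week floor would pass. Taken with the word recurrent in the aim, it naturally means an earlier episode.
- **Admitting chronic patients costs power.** No passage says that they respond less to movement control exercise, and the article reports benefit in mostly chronic samples. The effect sizes quoted under sub-classification (0.43 short term, 0.14 long term) concern classification-based treatment in general, not this comparison. The protocol states no standard deviation and no chronic share. If the effect is the same in both groups and the variability is unchanged, power is unchanged.

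**Conclusion.** The point holds as an internal inconsistency. The entry rule, as published, does not exclude patients whom the protocol defines as chronic, while the aim and Discussion describe a sub-acute population. A conclusion specific to sub-acute LBP is therefore not secured by the criteria.

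The size cannot be fixed from the documents. It depends on the share of participants beyond 3 months, which is not given, and it would be nil if the unseen screening material enforces the limit. Internal validity is unaffected. The consequence is confined to whom the result describes and to whom it can be applied. This should be fixed, but it is not a fatal flaw.

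**What to change.** Reconcile the Background definition, the aim, the Recruitment statement and the Inclusion criteria in one of two ways:

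1. If the sub-acute population is intended, write the protocol's own definition into the criterion for further enrolment: duration of at least 6 weeks and not over 3 months.
2. If longer durations are intended, remove sub-acute from the aim and conclusions and describe the population by the rule actually applied.

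In either case:

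- Keep every randomised patient in the primary analysis.
- Record episode duration at entry for all participants. For those already enrolled, take it from baseline records before outcomes are examined.
- Report the distribution of duration by arm.
- Pre-specify a supporting analysis in those within 6 weeks to 3 months. Duration at entry precedes randomisation, so the comparison within that subset is still randomised, but it will be imprecise if the subset is small.

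The first option may slow recruitment somewhat at a single clinic. Recruitment began in October 2010, so it also requires a documented mid-trial amendment and leaves two entry rules within a trial of 70. The second option costs no recruitment but gives up the claim to fill the evidence gap in sub-acute LBP. Recording duration adds one item to the baseline form.
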